### **14. Withdrawal of Participants**

Participants will be told that they can drop out of the study at any time during the study. Participants who become pregnant or become cognitively impaired throughout study duration will be withdrawn from the study without their consent. Furthermore, participants who become otherwise unable to participate in the research procedures due to health-related concerns will be withdrawn from the research without their consent at the discretion of the PI. Data collection will cease for participants who

[figure not shown]

withdraw from the research and these individuals will not be included in the final data analysis.

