## 2. Objectives

The purpose of this study is to evaluate the feasibility of enrolling adolescents into a prospective cohort study that uses ecological momentary assessment (EMA) and an activity tracker to quantify the effects of social isolation during the COVID-19 pandemic on mental and cardiovascular health. The objective is to collect pilot data on physical health metrics including physical activity, dietary patterns, sleep, and heart rate variability (HRV), along with measurements of social isolation, social connectedness, and

[figure not shown]

loneliness. These data will be used to apply for funding for a larger cohort study of the effects of social isolation on adolescent mental and cardiovascular health.

The specific aims are:

A1: Evaluate the feasibility of a prospective cohort study of social isolation in adolescence that utilizes ecological momentary assessment and activity tracking.

H1. A recruitment rate of 30% and a retention rate of 80% would indicate feasibility for a larger cohort study.

A2: To quantify the effects of social isolation on adolescent physical activity, dietary quality, sleep, and heart rate variability. Compared to adolescents who are less socially isolated, adolescents who are more socially isolated will have:

H2a: Lower physical activity as measured by an activity tracker

H2b: Less healthy diets as measured on by self-report

H2c: Later sleep onset and less consolidated sleep as measured by an activity tracker

H2d: Lower heart rate variability as measured by a heart rate monitor

A3: To identify factors that exacerbate or mitigate the effects of social isolation on adolescents. This exploratory aim will measure factors such as self-reported social connectedness, loneliness, social media use, adverse childhood experiences, peer victimization, discrimination, family cohesion, as well as sociodemographic factors including gender, race, family income, parental education, and neighborhood poverty level.

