## 4. Study Endpoints

The primary study endpoints are 1) feasibility (recruitment and retention rate) and 2) usability (% of days activity tracker is worn, % of EMA surveys completed, % of data that is interpretable). Secondary endpoints include objectively documented physical activity, sleep, self-reported diet, and heart rate variability.

[figure not shown]

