*Monitoring of Social Connectedness, Isolation, Loneliness, and Mood via EMA.* Following the approach of the MIDUS II National Study of Daily Experiences (NSDE), we will assess daily social connectedness, isolation, loneliness and negative/positive affect. Participants will randomly receive a text message four times per day for 14 days instructing them to complete the EMA surveys use an app called “RealLife Exp” which they will be instructed to download on their phone at the baseline visit. The RealLife Exp app is an iOS/Android app that will push notifications to participants’ mobile devices to alert them to complete daily surveys. Notifications will be pushed to the participants phone on a fixed schedule and participants will tap the notification allowing them to answer questions right away. The app will not collect any PHI and participants will be assigned a study ID which will help provide anonymity to participants when answering questions and allow the study team to link responses to other data collected on participants throughout the study. The study team will not be able to monitor any activity associated with participants’ mobile devices. The platform and data storage protocols for the app are HIPAA compliant. When subjects reach the end of the study duration, they will be instructed to remove the app from their phone. The research coordinator will walk participants through this process.

Participants will be sent a survey derived from the loneliness and distress questionnaire used by Yung et al, and containing questions surrounding overall connectedness. This survey will be sent to participants 4 times a day and will ask participants to rate these items based on their experiences over the past few hours. The survey will also contain questions surrounding passive and active social media use since social media has been associated with affect and social media use in youth and may or may not mitigate social isolation due to COVID-19.

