## **12. Local Number of Participants**

[figure not shown]

A total of 20 participants will be recruited for the study. All participants will be recruited from the CHOA Hughes Spalding Adolescent Medicine Practice. Using the social isolation questions found in the screening survey (ATTACHED), we will split participants into two groups for comparison: socially isolated (n=10) vs non-socially isolated (n=10)

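### Excluding everyone who withdraws from the final analysis conflicts with the primary retention and usability endpoints

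*Protocol*

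**What the plan says.** Section 14 (Withdrawal of Participants) sets the rule in one sentence, which a page break splits. "Data collection will cease for participants who" is followed by "withdraw from the research and these individuals will not be included in the final data analysis". The section covers two kinds of withdrawal. One is voluntary: "Participants will be told that they can drop out of the study at any time during the study". The other is withdrawal without the participant's consent, for pregnancy, cognitive impairment or other health reasons. No endpoint is exempted.

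Section 4 (Study Endpoints) makes the recruitment and retention rates primary, together with "usability (% of days activity tracker is worn, % of EMA surveys completed, % of data that is interpretable". Section 2 (H1) sets the decision rule: "A recruitment rate of 30% and a retention rate of 80% would indicate feasibility for a larger cohort study". Section 17 repeats the two thresholds.

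Section 12 fixes the size: "A total of 20 participants will be recruited for the study". Section 6 fixes the EMA schedule: "Participants will randomly receive a text message four times per day for 14 days".

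Section 18 provides for retention reports and for tracking of drop-outs, as part of data-quality review and IRB oversight. No section defines the denominator of the retention rate or of the usability percentages.

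**The concern.** A retention rate exists to count people who leave, and the exclusion rule takes those people out of the analysis. The usability percentages have a related problem. Someone who leaves during the 14-day monitoring period has a short record because collection stops, and that record is then dropped altogether.

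The loss is plausibly informative. Section 15 acknowledges that the devices may be uncomfortable or inconvenient and the questions embarrassing, and it reminds participants that they may withdraw. Exit because of burden is something a feasibility study needs to see.

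The result is meant to support an application for a larger cohort (Section 2), so an inflated rate would carry over into that study's planning. The Aim 2 comparison of isolated and non-isolated adolescents (10 against 10, Section 12) would also lose device and EMA data that had been validly collected.

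**Working it through.** The protocol reports no calculated figure for this point. Its power statement in Section 17 does not bear on it. The one number to check against is the 80% retention threshold, which with 20 enrolled means at least 0.80 × 20 = 16 retained, or at most four withdrawals.

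**Inputs from the protocol.** Enrolled: 20 (Section 12). Scheduled EMA prompts: 4 per day × 14 days = 56 per participant, and 20 × 56 = 1,120 in all (Section 6). Retention threshold: 80% (Sections 2 and 17).

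**Assumed, because the protocol gives no figures.** The number who withdraw (k), when they leave, and the completion rate while enrolled.

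**Retention.** On all enrolled it is (20 − k)/20. With Section 14 applied literally it is (20 − k)/(20 − k).

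| Withdrawals k | All enrolled | Section 14 read literally | 80% criterion on all enrolled |
|---|---|---|---|
| 2 | 18/20 = 90% | 18/18 = 100% | met |
| 4 | 16/20 = 80% | 16/16 = 100% | met |
| 5 | 15/20 = 75% | 15/15 = 100% | not met |
| 6 | 14/20 = 70% | 14/14 = 100% | not met |
| 8 | 12/20 = 60% | 12/12 = 100% | not met |

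From five withdrawals on, the two readings give opposite answers. Under the literal reading only loss without formal withdrawal could lower the rate.

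**EMA completion, early withdrawal.** Assume 80% completion while enrolled and exit after day 3, so 3 × 4 = 12 prompts are received before leaving.

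- k = 4, all enrolled over the scheduled 14 days: (16 × 56 × 0.8 + 4 × 12 × 0.8)/1,120 = (716.8 + 38.4)/1,120 = 755.2/1,120 = 67%.
- k = 6, same measure: (14 × 56 × 0.8 + 6 × 12 × 0.8)/1,120 = (627.2 + 57.6)/1,120 = 684.8/1,120 = 61%.
- Section 14 rule, either case: 80%. With k = 4 its denominator falls to 16 × 56 = 896 prompts.
- k = 4, over days enrolled: 755.2/(896 + 4 × 12) = 755.2/944 = 80%. Under this assumption the gap comes wholly from the prompts after withdrawal.

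**EMA completion, other exit patterns.** Let k = 4, let those who stay average 80%, and let those who withdraw complete a share f of the full 14-day schedule. The all-enrolled value is (16 × 0.80 + 4 × f)/20. The rule always gives 80%.

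| f | All enrolled | Rule minus all enrolled |
|---|---|---|
| 0% | 64% | +16 points |
| 20% | 68% | +12 points |
| 40% | 72% | +8 points |
| 80% | 80% | 0 |
| 100% | 84% | −4 points |

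The last two rows are possible when a participant finishes the 14 days and withdraws during the optional monthly follow-up. The rule then discards a finished record.

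**The case against.** Several points against the concern have force.

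- **Retention may be counted properly anyway.** An 80% threshold means little if leavers are outside the denominator. Section 18 ensures that drop-out counts will exist, and a sensible analyst would use them. This stands as an expectation of good practice. However, Section 18 describes monitoring, and nothing in the protocol links those counts to the endpoint. It also does nothing for usability or Aim 2.
- **Usability is not biased upward by construction.** A reader might infer that it is. The second table shows that the direction depends on when people leave and what they completed. Upward bias is expected for exit within the 14 days, but not for exit afterwards.
- **Usability cannot reverse the feasibility decision.** Only recruitment and retention have thresholds. An inflated EMA percentage would mislead readers but would not change the stated go/no-go result.
- **Withdrawal is not the only way usability fails.** Enrolled participants who ignore prompts or leave the tracker off stay in the analysis. Under Section 6 the coordinator texts anyone with no device data or no EMA response for 24 hours. So the rule does not remove every failure.
- **Scoring all prompts after withdrawal as failures is debatable.** It counts one event in both retention and usability, and it would treat investigator-initiated withdrawal as non-use. This is a good reason to report completion over days enrolled as well.
- **The Section 17 tests lose little from early exit.** Someone who leaves within the 14 days contributes no baseline-to-monthly pair in any case. For early leavers the harm is confined to the Aim 2 device and EMA data. It becomes selection bias only if leaving is related to isolation or burden.

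**Conclusion.** The concern holds. Section 14 states a rule without exception, and following it as written gives a wrong answer for the primary endpoints. This is a conflict within the protocol, not detail left to an analysis plan: a plan that computed these endpoints on all enrolled would have to contradict Section 14.

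For retention, the literal rule returns 100% of those not withdrawn whatever the number of withdrawals, and it hides a missed criterion from five of 20 on. For usability, with four withdrawals and 80% completion among those who stay, it overstates 14-day completion by 8 to 16 points if leavers completed 0% to 40% of the schedule. In the day-3 example the overstatement is about 13 points (80% against 67%). It makes no difference at 80% and understates by 4 points at 100%. All of the withdrawal and completion figures are assumptions.

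A reader might go further and infer that the study is bound to declare itself feasible. The documents do not support that. Retention can be counted from the drop-out log, recruitment has its own threshold, and non-use by participants who stay still counts.

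**What to change.** Replace the exclusion sentence in Section 14 with wording such as:

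> Data collection stops at withdrawal; data collected up to withdrawal are kept and analysed, as consent allows, unless the participant asks for removal. Retention is computed with all enrolled participants as the denominator. Usability is reported for all enrolled participants over the scheduled 14 days, and also over the days each participant was enrolled, with withdrawals listed by reason (voluntary or investigator-initiated).

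The cost is a protocol wording change and a check of the consent form, which may need a matching line if it promised exclusion. No new data are needed, since Section 18 already has drop-outs tracked. The reported rates may be lower than under the present rule.

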### **15. Risks to Participants**

The proposed study involves greater than minimal risk to children presented by a monitoring procedure which is not likely to contribute to the well-being of the subject. A potential risk/discomfort from participation in this study is the use of wearable devices. These devices may be uncomfortable or inconvenient for participants to wear for extended periods of time. Additionally, participants may feel uncomfortable or embarrassed when asked questions related to social connectedness, loneliness, social media use, adverse childhood experiences, peer victimization, and discrimination. To minimize these risks, participants will be given demonstrations on how to appropriately wear the devices and will be able to decline to answer questions they do not feel comfortable answering. Furthermore, participants may withdraw from the study at any time.

Another risk to participants is breach of confidentiality. To ensure participant confidentiality, study identification numbers will be assigned to each participant and used throughout the duration of the study when referring to subjects. The codes that link the name of the participant and the study identification number will be kept confidential by the PI in a secured cabinet. Only the authorized study team with appropriate training will have access to the data.

### **16. Potential Benefits to Participants**

Potential benefits to participants include increased awareness of personal health metrics (i.e. heart rate, physical activity, sleep) as reported by the activity tracker used in this study.

### **17. Data Management and Confidentiality**

Given our proposed sample size of 20 participants, we have at least 80% power to detect a 0.53 standard deviation change from baseline to 3 months on a given outcome measure using a two-sided paired t-test with an  $\alpha = 0.05$ . We will report descriptive statistics for the EMA assessments. Paired t-tests (or if data are not normally distributed, the Wilcoxon signed-rank test) will be used to compare the baseline and monthly survey data for the continuous scales. Results will be presented as difference in means or medians with associated 95% confidence intervals. McNemar's test for correlated proportions will be used to compare binary outcomes including the baseline and monthly follow up survey data. Effect sizes will be calculated for all measures to further quantify the degree of efficacy. A recruitment rate of 30% and retention rate of 80% would indicate feasibility for a larger trial. Statistical analysis will be conducted using SAS v. 9.4 (Cary, NC) and significance will be assessed at the 0.05 level.

All questionnaire data will be collected using REDCap software. Data related to wearable devices will be collected using the manufacturer's software. To maintain participant confidentiality, all participants will be assigned a study identification number. The codes

[figure not shown]

that link the name of the participant and the study identification number will be kept confidential by the PI in a secured cabinet.

Upon data storage, all data will be de-identified. Only the authorized study team on this proposal will have access to the data. All study staff will complete biomedical or socio-behavioral training through the Collaborative IRB Training Initiative Program (CITI). We will store the data on the Emory server. The server is protected by the Emory network, and a secured log-in is required from all users. Data will be stored only until final analysis and publication of any manuscripts, after which the data files will be removed. No data will be released to other agencies.

To ensure data quality, the research team will use REDCap validation methods throughout surveys to ensure that entered values are within the specified range and that items are not inappropriately skipped. Data from the wearables will be closely monitored by the study team on a weekly basis to ensure accuracy. Additionally, the research coordinator will routinely check in with the participant to ensure that they are wearing the devices correctly and answer any questions. All participants will receive a thorough demonstration on how to sync, wear, and charge devices.

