| Secondary Objective(s)                     | 

1. To quantify the effects of social isolation on adolescent mental and cardiovascular health metrics including physical activity, dietary quality, sleep, and heart rate variability

2. To identify factors that exacerbate or mitigate the effects of social isolation on adolescents during the COVID-19 pandemic

 |
| Research Intervention(s)/Interactions      | Study subjects will complete surveys using ecological momentary assessment and will wear an activity tracker which will measure physical activity, sleep, and heart rate variability                                                                                                                                                                                         |
| Study Population                           | Adolescents ages 13-18 years of age                                                                                                                                                                                                                                                                                                                                          |
| Sample Size                                | 20                                                                                                                                                                                                                                                                                                                                                                           |
| Study Duration for individual participants | 14 days, with option to continue to be contacted for up to 12 months                                                                                                                                                                                                                                                                                                         |

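### Twenty participants give about 61% power, not 80%, for a 0.53 SD paired change; 0.53 SD is the detectable change for 30 complete pairs

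*Protocol*

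**What the plan says.** The only power statement in the protocol is in Section 17. It starts from the planned enrolment ("Given our proposed sample size of 20 participants"), claims that "we have at least 80% power to detect a 0.53 standard deviation change from baseline to 3 months" for any one outcome, and names the method: "using a two-sided paired t-test" at alpha 0.05. The same section plans paired comparisons of baseline with the monthly survey scores.

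Three other places bear on how many pairs there will be:

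- Section 12: "A total of 20 participants will be recruited for the study". No extra recruitment is planned to cover losses.
- Section 1 gives each participant's duration as "14 days, with option to continue to be contacted for up to 12 months". Section 6 (Study End) confirms that monthly surveys go only to those who agree to continue.
- Section 2, hypothesis H1: "A recruitment rate of 30% and a retention rate of 80% would indicate feasibility for a larger cohort study".

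Section 14 adds that participants who withdraw are left out of the final analysis.

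**The concern.** Section 17 states every input that a paired t-test calculation needs, so the claim can be checked directly. A detectable change of 0.53 SD looks too small for 20 pairs.

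The pilot data are meant to support a funding application for a larger cohort (Section 2). A reader who trusts Section 17 would believe that a true change of 0.53 SD is missed at most 20% of the time. If the miss rate is well above that, a null result on one of the paired comparisons says less than the protocol implies. An applicant reusing the sentence would also carry the error into the next study.

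**Working it through.** **Inputs, all from Section 17:** n = 20 pairs; change d = 0.53 SD; two-sided paired t-test; alpha = 0.05; stated power at least 80%.

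**Method.** A paired t-test is a one-sample t-test on the within-person differences. With d in units of the SD of those differences, the test statistic follows a noncentral t distribution with n − 1 degrees of freedom and noncentrality d × √n. Power is the probability that its absolute value exceeds the 0.975 quantile of the central t.

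**1. The stated figure at n = 20.**
- Noncentrality: 0.53 × √20 = 2.370. Critical value on 19 df: 2.093.
- Power = **61.4%**. A simulation with 400,000 replicates gives 61.5%.
- The stated 80% is not reproduced; the shortfall is 80 − 61.4 = 18.6 percentage points.

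**2. The change detectable with 80% power at n = 20.** Solving for d gives **0.660 SD**.

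**3. The sample size that matches 0.53 SD.**

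| Complete pairs | Power at 0.53 SD | Change detectable with 80% power |
|---|---|---|
| 16 | 51% | 0.749 SD |
| 20 | 61.4% | 0.660 SD |
| 29 | 78.7% | 0.539 SD |
| 30 | 80.1% | 0.529 SD |

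Thirty is the smallest number of pairs that reaches 80%, and its detectable change rounds to the printed 0.53.

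**4. Could another method have produced 0.53 at n = 20?**

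| Reading at n = 20 | Power at 0.53 SD | Detectable with 80% power |
|---|---|---|
| Two-sided, normal approximation | 65.9% | 0.626 SD |
| One-sided t (same as two-sided alpha 0.10) | 73.9% | 0.577 SD |
| One-sided, normal approximation | 76.6% | 0.556 SD |
| Two-sample t, 10 v 10 | 20.2% | – |
| Two-sample t, 20 v 20 (40 in all) | 37.2% | – |

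None reaches 80%, and the text specifies a two-sided paired test in any case.

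**5. The 0.53 read as SDs of the raw score.** If the SD is the same at both times and the correlation between them is ρ, the SD of the difference is SD × √(2(1 − ρ)). The detectable raw change is then 0.660 × √(2(1 − ρ)):
- ρ = 0.3: 0.660 × √1.4 = 0.78 raw SD (power at 0.53: 48%)
- ρ = 0.5: 0.660 × √1.0 = 0.66 raw SD (power 61%)
- ρ = 0.7: 0.660 × √0.6 = 0.51 raw SD (power 83%)

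Setting the result to 0.53 gives ρ = 1 − (0.53/0.6604)²/2 = 0.678. These correlations are assumed values; the protocol gives none.

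**6. Fewer than 20 pairs.** At the H1 benchmark, 0.80 × 20 = 16 pairs. Noncentrality is 0.53 × √16 = 2.12 against a critical value of 2.131 on 15 df, which gives 51% power and a detectable change of 0.75 SD. This is a sensitivity case, since the protocol does not forecast how many participants will have both values.

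**The case against.** The strongest reply is that Section 17 does not say which SD it means. If it is the SD of the measure itself, the claim can be true: at a correlation of 0.7 between baseline and 3 months, 20 pairs give 83% power. That is arithmetically right, and it makes the 61% conditional on reading 0.53 in units of the SD of the paired differences, the standard scale for this test. It does not rescue the sentence. The claim is unconditional and covers any outcome measure, so it would need every scale to reach an unstated correlation of about 0.68.

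Other points narrow the finding without removing it:

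- The 80% retention figure is a benchmark for judging feasibility, not an attrition assumption. The 16-pair result is therefore only a sensitivity case. The error at n = 20 does not depend on it.
- Section 9 describes participants who decline the monthly surveys as enrolled for three months, which might suggest 3-month data from everyone. The measures table in Section 6 lists no 3-month assessment apart from the optional monthly surveys.
- The protocol nowhere mentions 30 participants. That 0.53 came from a calculation for 30 is inferred from the numerical match.
- The primary objective is feasibility, no decision rule uses this power figure, and Section 17 promises confidence intervals and effect sizes, which will show the imprecision. This limits the practical harm. It does not make the stated figure correct.

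**Conclusion.** The power statement is wrong on its own inputs. With 20 complete pairs, a two-sided paired t-test at alpha 0.05 has 61.4% power for a change of 0.53 SD of the paired differences, so such a change would be missed about 39% of the time rather than at most 20%. Eighty per cent power is reached at 0.66 SD with 20 pairs, or at 0.53 SD with 30.

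The result assumes normally distributed differences and the SD-of-differences scale. On the raw-score scale the claim would need a correlation of about 0.68 or more, which the protocol neither states nor supports. Any missing 3-month values lower the power further, to about 51% with 16 pairs.

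Because this is the protocol's only power claim and it is demonstrably incorrect, it must be corrected. The feasibility aim and its criteria are unaffected.

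**What to change.** Replace the power sentence in Section 17 with wording such as: *With 20 complete pairs there is 80% power (two-sided paired t-test, alpha 0.05) to detect a change of 0.66 SD of the paired differences; with 16 complete pairs the detectable change is 0.75 SD.* Delete the 0.53 figure. Naming the SD of the paired differences removes the ambiguity of scale, and referring to complete pairs makes clear that only participants with both values count.

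The cost is one edited sentence and a less favourable stated figure. No further recruitment is needed for a feasibility study. If the team wished to keep 0.53 SD at 80% power, it would need 30 complete pairs, which at 80% retention means 30 / 0.80 = 37.5, so 38 enrolled.

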In contrast to the data on mental health, the connection between social connection, social isolation, and loneliness and cardiovascular health across the life course is only beginning to be understood. In animal models, socially isolated animals develop more atherosclerosis than those housed in groups. In the few studies done with youth, children who were socially isolated from their peers had less optimal cardiovascular health metrics at 26 year of age and higher levels of inflammation as measured by c-reactive protein in midlife. In adults, social isolation and loneliness are associated with elevated c-reactive protein and later cardiovascular disease (CVD) death, as well as incident CVD events including a 29% increase in risk of incident coronary heart disease (CHD) and a 32% increase in risk of stroke, and future mortality in those with established CVD. Together, these studies establish a relationship between social connectedness, isolation, and loneliness and cardiovascular health while posing important unanswered questions about mechanisms, key developmental periods in the life course, and the impact of unique stressors such as the COVID-19 pandemic.

Potential mechanisms linking loneliness and social isolation with cardiovascular health include increased peripheral vascular resistance, increased inflammation and dysregulated HPA-axis activity. One established mechanism for assessing the impact of all of these systems on cardiovascular health is heart rate variability (HRV) as it reflects a complex interplay between the physiologic, cognitive, and emotional regulatory systems. In general, greater HRV is associated with greater capacity to respond to physical and emotional stress. HRV changes during adolescence, from the relatively higher HRV of childhood to the relatively lower HRV of adults.

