**Study End.** Participants will be contacted by the CRC to document their consent to continue to be contacted for monthly surveys administered via use the “RealLife Exp” application. Participants who do not wish to continue will be instructed in how to remove the application from their phone. Participants who decide to be contacted for monthly surveys will continue to use the RealLife Exp app and receive notifications to complete EMA surveys once per month. After one year of follow-up for those consenting to the monthly EMA surveys, participants will be instructed in how to remove the application from their phone. No data will be collected after 1 year. Participants will be contacted via phone once more by the CRC for a semi-structured interview about their perspective on the study and its requirements. The CRC will also access their chart to view the date and time of their future appointments in the Adolescent Clinic at Children’s Healthcare of Atlanta at Hughes Spalding. Once participants come into the clinic for their appointment, the CRC will approach them to gauge their interest in the interview. If participants agree to participate in the interview, their answers will be collected as part of assessing the feasibility of the study.

All participants will be given a pre-addressed, stamped envelope in which to return the activity tracker and heart rate monitor after the 14-day study duration. No additional data will be collected from participants using these devices after the 14-day period.

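### The tests and power statement in section 17 concern paired change over time, whereas Aim 2 compares isolated with non-isolated adolescents

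*Protocol*

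**What the plan says.** **The question.** Section 2 introduces H2a to H2d with "Compared to adolescents who are less socially isolated, adolescents who are more socially isolated will have", followed by lower tracker-measured activity, less healthy self-reported diet, later and less consolidated tracker-measured sleep, and lower heart rate variability (HRV) from the heart rate monitor. Section 12 sets up the groups: "we will split participants into two groups for comparison: socially isolated (n=10) vs non-socially isolated (n=10".

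**The analysis.** Section 17 holds the protocol's statistical text. Paired t-tests, or Wilcoxon signed-rank tests if the data are not normal, "will be used to compare the baseline and monthly survey data for the continuous scales". McNemar's test is named for binary outcomes. EMA data are to be described. Effect sizes are promised for all measures, with no contrast defined. On power: "we have at least 80% power to detect a 0.53 standard deviation change from baseline to 3 months on a given outcome measure". The test assumed there is the paired t-test, two-sided, at 0.05.

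**The data.** The Study Measures table in section 6 lists actigraph activity, actigraph sleep and HRV only in the During Study column. Under Study End, section 6 adds: "No additional data will be collected from participants using these devices after the 14-day period". Self-reported diet appears both at baseline and in the monthly surveys. The monthly surveys are optional (sections 1 and 6).

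**The concern.** A paired test needs two measurements of the same outcome on the same person. A group contrast needs one outcome measurement per person and a group label. Section 17 provides for the first, and Aim 2 asks for the second. The two groups of section 12 do not appear in section 17 at all.

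Two things are at stake. First, an analyst who applied only the named tests would not produce the comparison in H2a to H2d. Change over calendar months in the whole sample says nothing direct about isolated against non-isolated participants. Second, the power sentence refers to any given outcome measure, so a reader may take the study to be well powered for moderate differences on the Aim 2 outcomes. Section 2 says the pilot data will support a funding application for a larger cohort, where a realistic statement of precision for this contrast matters.

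**Working it through.** **Step 1. Can the named tests be applied to each hypothesis?**

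| Hypothesis | Source (section 2) | When measured (section 6) | Paired test possible? | Would it address Aim 2? |
|---|---|---|---|---|
| H2a activity | tracker | one 14-day period | no | – |
| H2b diet | self-report | baseline and monthly | yes | no, it measures change over time |
| H2c sleep | tracker | one 14-day period | no | – |
| H2d HRV | heart rate monitor | at least 24 hours, up to 14 days, once | no | – |

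Self-reported physical activity is also repeated monthly, but H2a specifies the tracker.

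**Step 2. The plan's own figure.** Inputs from section 17: n = 20, change 0.53 SD, two-sided alpha 0.05, paired t-test.

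- Noncentrality = 0.53 × √20 = 2.37, with 19 degrees of freedom.
- Power from the noncentral t = 61.4% (normal approximation 65.9%).
- The change detectable with 80% power at n = 20 is 0.66 SD; 0.53 SD corresponds to n = 30 (80.1%).

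The stated 80% is therefore not reproduced if 0.53 is in units of the SD of the change. It would hold if 0.53 were in units of the outcome SD and the correlation ρ between baseline and 3 months were high enough: 0.53 / √(2(1 − ρ)) = 0.66 gives ρ of about 0.68. The protocol states neither. This is a separate matter; the present point does not depend on it.

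**Step 3. The Aim 2 contrast.** Inputs: 10 vs 10 (section 12), two-sided 0.05 (section 17), unadjusted two-sample t-test, 18 degrees of freedom, critical value 2.101. Differences are in units of the between-person outcome SD.

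- Power at 0.53 SD: noncentrality = 0.53 × √(10 × 10 / 20) = 0.53 × 2.236 = 1.185, so power = 20.2% (normal approximation 21.9%).
- Difference detectable with 80% power: 1.32 SD (normal approximation 1.25).
- Expected 95% CI half-width: 2.101 × √(1/10 + 1/10) = 2.101 × 0.447 = 0.94 SD.
- Size needed for 80% power at 0.53 SD: 57 per group.

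**Step 4. Sensitivity to loss.** If retention were exactly the 80% target, and the loss fell equally on the two groups and removed device data (both assumptions of mine), 8 vs 8 would remain and the detectable difference would be 1.51 SD.

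**The case against.** The strongest reply is that this is a 20-person feasibility pilot. Its primary endpoints (section 4) are recruitment, retention and usability, and none of them rests on a paired or a group test. That stands, and it limits the severity.

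A second reply is that the test for a secondary aim may be left to an analysis plan, that section 12 announces a comparison, and that section 17 promises effect sizes for all measures. Part of this stands: nothing forbids a group comparison, and the data to make one are collected. A reader might infer that the study cannot estimate its second aim; the documents do not support that. But this is not mere silence. The protocol commits to tests and a power figure for a different question, and its effect-size sentence does not say which contrast is meant.

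Three further readings go too far:

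- **That every Aim 2 outcome is measured only once.** Diet is self-reported and repeated monthly.
- **That 20% power refutes the quoted 80%.** One figure is for a difference between persons, the other for a change within persons. The protocol never claims 80% for the group contrast, so this comparison shows no miscalculation.
- **That age confounds the HRV result.** Section 3 says "HRV changes during adolescence, from the relatively higher HRV of childhood to the relatively lower HRV of adults", and enrolment spans 13 to 18 years, but nothing shows that the two groups will differ in age. Confounding is possible, not established.

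**Conclusion.** The point holds as a mismatch between the stated analysis and Aim 2. The named tests cannot be run on H2a, H2c or H2d, and on H2b they answer another question. The power sentence does not apply to Aim 2.

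For the planned groups, a 95% CI would extend about 0.94 SD either side of the estimate, and only a difference of about 1.32 SD would be detected with 80% power. These figures assume full device and diet data on all 20 participants, an exact 10 vs 10 split, roughly normal outcomes with equal variances, and no covariate adjustment. They do not carry over directly to an adjusted model or to isolation used as a continuous score.

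Severity is moderate. The feasibility conclusion does not depend on any of this.

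**What to change.** In section 17:

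1. State that Aim 2 is analysed as the difference between the isolated and non-isolated groups in each 14-day device summary (activity, sleep onset, sleep consolidation, HRV) and in the baseline diet score, each reported with a 95% CI. Age adjustment can be an optional sensitivity analysis; with 20 participants it need not be the main one.
2. State the expected precision for that contrast: a half-width of about 0.94 SD and, separately, a detectable difference of about 1.32 SD, both for the unadjusted 10 vs 10 comparison.
3. Say that the existing power sentence concerns only paired survey change among participants who opt in to monthly follow-up.
4. Keep the paired and McNemar tests as an exploratory description of the monthly surveys.

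This is a rewording that uses data already planned. The cost is a less favourable statement of what the study can show on its second aim.
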